##### Behaviour change

Accelerometry will be used to objectively measure weekly minutes of light, moderate and vigorous physical activity at baseline and immediately post-intervention. Data will be collected using the ActiGraph (ActiGraph GT3X, http://www.theActiGraph.com) accelerometer, which will be worn on the right hip during waking hours for 7 days with the intention of gaining at least 5 days of usable data [54]. Participants will record times the monitor was removed and wear-time will be validated using Choi et al. [64]. Triaxial data will be collected in 1-s epochs along with step counts and inclinometry. The adapted Godin leisure-time questionnaire will be used to assess self-reported aerobic and resistance based physical activity at baseline and immediately post-intervention [12]. Finally, at the immediate post-intervention follow-up only, self-rated exercise adherence will be measured using two items with an 11-point numeric rating scale (0 = strongly disagree, 10 = strongly agree). Participants will be asked to separately rate their agreement with two statements related to their adherence to their prescribed programme (overall aerobic exercise sessions, overall resistance exercise sessions) [58].

##### Health outcomes

All health-related outcomes will be assessed at baseline and immediately post-intervention. Health-related quality of life will be assessed using the EORTC Quality of Life-Core 30 (EORTC QLQ-C30), which is a validated and reliable questionnaire for quality of life in cancer patients [65]. The 30-item core survey assesses a comprehensive range of quality of life domains including functioning (physical, role, cognitive, emotional and social), symptoms (fatigue, nausea and vomiting, sleep, pain, appetite, shortness of breath), financial hardship and global health status [59].

The 13-item Functional Assessment of Chronic Illness Therapy-fatigue subscale will be administered to measure participant’s level of fatigue. The questionnaire has been demonstrated as a valid and reliable measure [60]. The Hospital Anxiety and Depression Scale will be used to evaluate changes in anxiety and depression by using two 7-item Depression and Anxiety sub-scales [61]. The reliability and validity has been shown to be acceptable in individuals with prostate cancer [66]. Additionally, the Pittsburgh Sleep Quality Index questionnaire will measure sleep quality. Psychometric evaluation of the Pittsburgh Sleep Quality Index in cancer patients has established internal consistency, reliability and construct validity [62].

#### Intervention mechanisms

The proposed behavioural change mechanisms will be assessed at baseline and week 9. This will include measuring barrier self-efficacy for resistance and aerobic activities (9 items [55]), outcome expectations (8 items [67]), motivation type (19 items [56]). Social support (2 items [55]), intentions (4 items [57]), behavioural capability (7 items [52] and habit formation (4 items [43]). Collection of this data will provide preliminary insight into if the intervention is working as expected and will also provide useful information for directing further tailoring efforts (e.g. by allowing us to examine how variable individuals are in these variables at baseline, and thus the extent of tailoring that is needed). Collection of this information will also be useful for establishing feasibility of collecting data needed for a formal mediation analysis in the main trial.

#### Sub-study outcome measures

Subgroup selection will be based on proximity to available testing sites, with all participants (both intervention and waitlist control groups) who can easily access one of our testing sites invited to complete subgroup measures). We intend to have testing sites available in Adelaide (the University of Adelaide, University of South Australia) and Melbourne (University of Melbourne).

##### Physical function

The 400-m walk will be used to assess aerobic fitness level [14, 68]. Participants will be asked to complete the walk as fast as they complete 20 laps of 20-m track. Measures of completion time (in seconds), maximal heart rate, average heart rate and rate of perceived exertion will be recorded. The timed up-and-go test and the repeated chair stand (5 repetitions) will be measured by time to completion to provide muscular power, ambulation and functional lower limb strength [12, 13, 63].

##### Muscular strength

The one-repetition maximum method will be utilised to determine muscular strength [14]. The leg extension will be used to determine lower limb strength, and the chest press will assess upper limb strength. Patients with proximal femur bone lesions will be excluded from the leg extension one-repetition maximum test, whereas those with rib, thoracic spine lesions and or humerus lesions will be excluded from the chest press one-repetition maximum test.

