**Fig. 2 Fig2:**
[figure not shown]
Study flow diagram

To be eligible, participants must have been diagnosed with metastatic prostate cancer (as confirmed by their physician) and have medical clearance from their physician (General Practitioner, Medical Oncologist, Radiation Oncologist or Urologist). Physicians are required to provide details regarding the extent and location of metastases. Participants also need to have access to a computer with the internet, be able to read and write in English and provide written consent prior to baseline testing. Finally, to be eligible participants should not already engage in two sessions of resistance-training and 60 minutes of structured moderate-vigorous aerobic exercise per week. Participants meeting one target but not the other will be eligible.

Patients will be deemed ineligible if they have any absolute contraindications to performing moderate physical activity (resistance, aerobic and flexibility) for at least 20 min (in bouts of 5 min), up to 2 days of the week. This includes no recent serious cardiovascular events (within 12 months), unstable bone metastases, spinal compressions or acute illness and infection [36]. Participants will also be excluded from the study if they have moderate to severe bone pain (Common Terminology Criteria for Adverse Events V.5.0 grading criteria).

Participant retention strategies will include flexible scheduling for telehealth consultations, reminder calls/texts and consistent study staff. Criteria for discontinuing intervention include participant request and worsening conditions which are absolute contraindications to exercise (including unstable bone metastasis, spinal compression and significant cardiovascular events). Concomitant care will be permitted during the study and any changes in treatment will be recorded.

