##### Web-based exercise prescription

Participants are individually prescribed an 8-week multi-modal (resistance, aerobic and flexibility) programme based upon the conservative prescription used in Galvão et al. (Table 2) and isometric spinal exercise prescription applied in Rief et al. [14, 15]. Exercise prescription variables can be autoregulated by re-completing module assessment questions using the links on the homepage. The intensity or volume of session regulated can be modified by participants modifying their fatigue ratings, pain levels and confidence. Resistance exercises which produce pain can also be changed by adjusting the movement-based questions (e.g. Do you experience pain when you bend or straighten your elbow whilst holding a heavy item?). Participants are educated on autoregulation via the safety and exercise plan modules and programme modification through computer-tailoring is discussed in the initial tele-coaching session).

**Table 2 Tab2:** Modified multimodal exercise prescription for individuals with bone metastases [14]

Metastasis Location	Resistance			Aerobic		Flexibility
	Upper	Trunk	Lower	WB	NWB	
Proximal humerus		^✓^	^✓^	^✓^	^✓^	^✓d^
Cervical spine	^✓a^		^✓^	^✓^	^✓^	^✓c^
Thoracic spine/ribs	^✓a^		^✓^	^✓^	^✓^	^✓c^
Lumbar spine	^✓^		^✓^		^✓^	^✓c^
Pelvis	^✓^	^✓^	^✓b^		^✓^	^✓c^
Proximal femur	^✓^	^✓^			^✓^	^✓e^

*WB* weight bearing (walking); *NWB* non-weight bearing (water walking; cycling)

^✓^Target exercise region

^a^Exclusion of shoulder flexion/extension/abduction/adduction—inclusion of elbow flexion/extension

^b^Exclusion of hip extension/flexion—inclusion of knee extension/flexion

^c^Exclusion of spinal flexion/extension/rotation

^d^Exclusion of elbow flexion/extension

^e^Exclusion of knee flexion/extension

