### Waitlist control group

Participants randomised into the wait-list control group will complete the baseline outcome measures as seen in Table 5 and will then be asked to continue with usual care, including maintaining their current physical activity levels for 8 weeks. In week nine, wait-list control participants will repeat the outcome measures. At the end of the intervention, the control group will be sent therabands, given access to the eHealth tool for 8 weeks, complete two tele-coaching sessions and receive weekly contact from an exercise physiologist as authors felt it was unethical to deny participants access to supported treatment.

**Table 5 Tab5:** Overview of measurement tools (page 17)

Outcome	Measure	Number of items	Intervention group	Control group	Collection point (week)
Acceptability	Module ratings	10	✓	x	1-8
	Website perceived personal relevance [52]	3	✓	x	9
	Client Satisfaction Questionnaire [34]	8	✓	x	9
	Perceived Environmental Supportiveness Scale [53]	15	✓	x	9
	Qualitative data (open-ended survey questions and qualitative interview)	4	✓	x	9
Usability	Software usability scale [35]	9	✓	x	9
Usage	Website usage data [54]	3	✓	x	1-8
	Number of exercise sessions	2	✓	x	1-8
Adverse events	Common Terminology Criteria for Adverse Events V.5.0 grading criteria	1	✓	✓	9
Mechanisms of action	Self-efficacy [55]	9	✓	✓	0, 9
	Outcome expectations [55]	8	✓	✓	0, 9
	Motivation type [56]	19	✓	✓	0, 9
	Social Support [55]	2	✓	✓	0, 9
	Intention [57]	4	✓	✓	0, 9
	Behavioural capability [52]	2	✓	✓	0, 9
	Habit formation [43]	4	✓	✓	0, 9
Behaviour change	ActiGraph Accelerometer [54]	1	✓	✓	0, 9
	Modified Godin-Leisure time questionnaire [12]	4	✓	✓	0, 9
	Self-rated exercise adherence [58]	2	✓	x	9
Health outcomes	European Organisation for Research and Treatment of Cancer Quality of Life-Core 30 [59]	30	✓	✓	0, 9
	Functional Assessment of Chronic Illness Therapy-fatigue subscale [60]	13	✓	✓	0, 9
	Hospital Anxiety and Depression Scale [61]	10	✓	✓	0, 9
	The Pittsburgh Sleep Quality Index [62]	14	✓	✓	0, 9
Sub-study physical function	400 m self-paced walk [14]	1	✓	✓	0, 9
	Timed up-and-go test [12]	1	✓	✓	0, 9
	Repeated chair stand [63]	1	✓	✓	0, 9
	One-repetition maximum [14]	2	✓	✓	0, 9

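### Cervical spine lesions are missing from the chest-press one-repetition-maximum exclusion, although Table 2 bars the same shoulder movements for them as for the excluded thoracic spine and rib lesions

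*Protocol article*

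**What the plan says.** The Muscular strength section names two maximal tests, leg extension for the lower limb and chest press for the upper limb, and sets lesion-site exclusions for each. For the lower limb: "Patients with proximal femur bone lesions will be excluded from the leg extension one-repetition maximum test". For the upper limb: "whereas those with rib, thoracic spine lesions and or humerus lesions will be excluded from the chest press one-repetition maximum test".

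Table 2, under Web-based exercise prescription, sets out which body regions may be trained for each metastasis location. In its upper-body resistance column, cervical spine and thoracic spine/ribs both carry footnote a: "Exclusion of shoulder flexion/extension/abduction/adduction—inclusion of elbow flexion/extension". Proximal humerus has no upper-body entry at all. In the lower-body column, pelvis carries footnote b, "Exclusion of hip extension/flexion—inclusion of knee extension/flexion", and proximal femur is blank.

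Testing is offered, in both arms, to all those "who can easily access one of our testing sites invited to complete subgroup measures" (Sub-study outcome measures). Table 5 schedules the item "One-repetition maximum" for both arms at weeks 0 and 9. Participants and screening excludes, among others, people with "unstable bone metastases, spinal compressions or acute illness and infection", and also those with moderate to severe bone pain. It requires physician clearance and adds: "Physicians are required to provide details regarding the extent and location of metastases".

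**The concern.** The chest-press list covers thoracic spine, ribs and humerus but leaves out the cervical spine, the only other site for which Table 2 restricts upper-body resistance work. A chest press loads the shoulder, and footnote a removes shoulder loading for cervical lesions in the same terms as for thoracic and rib lesions. The plan therefore allows a maximal effort in a movement that it bars at lower loads for the same person.

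What is at stake is participant safety in the sub-study. Safety is one component of the trial's primary feasibility outcome, and the Introduction itself names pathological fracture and neurological impairment as consequences of bone metastases. The exposure also reaches wait-list participants, who are tested twice without training in between.

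**Working it through.** The plan states no figure on this point, so there is none to reproduce. The check sets the resistance columns of Table 2 beside the exclusions in Muscular strength, site by site. It takes from general anatomy, not from the article, that a chest press requires loaded shoulder movement and a leg extension requires loaded knee extension.

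| Site (Table 2) | Upper-body entry | Chest press excluded? | Agree? | Lower-body entry | Leg extension excluded? | Agree? |
|---|---|---|---|---|---|---|
| Proximal humerus | none | yes | yes | allowed | no | yes |
| Cervical spine | footnote a (elbow only) | **no** | **no** | allowed | no | yes |
| Thoracic spine/ribs | footnote a (elbow only) | yes | yes | allowed | no | yes |
| Lumbar spine | allowed | no | yes | allowed | no | yes |
| Pelvis | allowed | no | yes | footnote b (knee kept) | no | yes |
| Proximal femur | allowed | no | yes | none | yes | yes |

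- Chest press: 5 of 6 sites agree. Leg extension: 6 of 6 agree. Together 5 + 6 = 11 of 6 × 2 = 12, with one mismatch, cervical spine by chest press.
- Table 2 rules out the tested movement in only four combinations: chest press for humerus, cervical spine and thoracic spine/ribs, and leg extension for proximal femur. Three of these four are excluded from testing. In the other eight, Table 2 does not bar the movement and the test is open.
- The pelvis row helps in reading the pattern. Table 2 restricts the lower body there but keeps knee extension, and the leg-extension test is accordingly left open.

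Entry screening: a person with a stable cervical lesion, no spinal compression, at most mild bone pain and a physician's clearance is eligible. If that person lives near a testing site and has no thoracic, rib or humerus lesion, nothing in the text stops the chest press.

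Load: the Resistance-based component section prescribes training at 8- to 12-repetition maximum, with each movement phase slowed to limit peak skeletal forces. A one-repetition maximum is by definition heavier than either.

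Exposure: one chest-press test at each of two visits gives up to 1 × 2 = 2 maximal tests per affected participant, in either arm.

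**The case against.** The strongest reply is that no stated rule is broken. Table 2 governs a conservative home programme, the exclusions govern a test at university sites, and nothing says that one must follow the other. The chest-press list is also not a transcription of Table 2: it says humerus where the table says proximal humerus, so the omission of cervical spine need not be a slip. Only four of the 12 combinations are informative, which is thin evidence for a site-by-site rule. Both Table 2 and the strength-test method cite the same earlier trial, which is not at hand and might justify testing these participants. Physician clearance and the exclusion of unstable lesions, spinal compression and more than mild bone pain reduce the risk, and the test serves only an exploratory outcome in an invited subgroup.

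Much of this stands as a limit. The link between the two sections is an inference, a deliberate choice cannot be ruled out, and 11 of 12 describes a pattern, not an impact.

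It does not explain the gap. A maximal test is not milder than training, so a movement barred in training needs a reason to be allowed in the test. The same entry screen protects people with thoracic, rib, humerus and femur lesions, yet the authors still judged site-specific test exclusions necessary for them. Nor is this detail left to a fuller document: the article states a specific exclusion list, and the objection is to what that list contains.

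**Conclusion.** The concern holds. The chest-press exclusion covers two of the three sites for which Table 2 restricts upper-body resistance work and leaves out cervical spine without explanation; it is the only mismatch across both tests. The consequence is up to two maximal chest presses per affected participant, in either arm.

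How many people this concerns cannot be derived from the article. The conclusion rests on the chest press being a shoulder-loading movement and on the view that a maximal test should be no more permissive than training for the same lesion. It bears on sub-study safety and on who contributes chest-press data, and should be fixed before testing continues.

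**What to change.** In Muscular strength, insert *cervical spine* at the head of the list of lesion sites excluded from the chest-press test, so that it covers cervical spine, thoracic spine, rib and humerus lesions. If the clinical team does intend to test people with cervical lesions, state the reason in the same place.

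The change is two words in one sentence. Physicians already report lesion locations, so no new data are needed, and the leg extension, the other function tests and the sample size are untouched. The cost is slightly fewer chest-press measurements.

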### Data management and monitoring

All research data will be stored on a password-protected network drive on a password-protected computer and only members of the study team will have access to this data. Questionnaire data will be recorded using a secure online data collection instrument (RedCap) with participants being sent web links at the appropriate time points. Participant contact information and name will be held in a separate file to study data, and unique ID numbers will be allocated. Only ID numbers will appear alongside outcome data. A trial steering committee (CES, DG, GK, NB) will oversee the trial. Any adverse events will be reported to the committee and the steering committee have the power the terminate the study if necessary. As a clinical oncologist and urologist sit on the trial steering committee, it was determined that a trial data monitoring committee was not required. Trial results will be submitted for publication and communicated in a relevant medical or scientific journal.

### Data analysis

#### Sample size

As this is a pilot study, which uses pre-specified criteria for success rather than a primary outcome, a formal sample size calculation was not essential [69]. Similar 2-arm pilot studies have reported sample sizes of 36 and 30 per arm for dichotomous and continuous endpoints, respectfully [70]. Similar to these studies, the enrolment target for this trial is 66 participants, 33 in each arm. Using a sample size calculation method created for pilot studies by Vichtbauer al., it was determined that the above sample size will allow us to identify feasibility problems (drop out, safety issues etc.) with a reasonable probability of occurring (i.e. a probability of 10% or greater), with a 95% level of confidence [71]. If issues are detected the trial team will review and consider if progression to a larger trial is warranted and feasible.

Study data will be analysed using SPSS version 26 (IBM, Chicago, IL, USA). Descriptive statistics will be calculated for all study variables. ANCOVAs (or non-parametric equivalents) will be used to conduct between-group comparisons, with potential confounders included in the model (e.g. age, time since diagnosis, treatment status and baseline outcome assessments). Treatment effects will be estimated as covariate-adjusted mean differences between the two treatment groups at follow up. A senior University of Adelaide statistician employed by the Freemasons Foundation Centre for Men’s Health will oversee the analyses. Sensitivity analyses will be conducted to explore the impact of missing data and remove any individuals who were unable to be prescribed with exercise from the analysis.

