### Pre-established criteria

Feasibility of conducting a larger-scale evaluation will be interpreted based on the following:
The recruitment goal has been reached (66 participants in 10 months).Behaviour change data are collected for ≥ 75% of participants recruited within the study.Physical functioning data (collected on a subset of participants) can be collected for ≥ 75% of participants that (a) reside within 30 km from a study testing site and (b) are invited to complete testing.

The success of the intervention will be interpreted based on the following:
The acceptability of the intervention is satisfactory (score of ≥ 20 on the client satisfaction questionnaire) [34].The system usability is satisfactory (score of ≥ 68 on the software usability scale) [35].There is no grade 3+/life threatening or severe adverse events attributed to participating in the intervention using the Common Terminology Criteria for Adverse Events V.5.0 grading criteria.There is evidence of meaningful participation in either aerobic activity and or resistance-based activity in the intervention group relative to the wait-list control. As the exercise prescription will be personalised, it is difficult to specify an average cut-point; however, we anticipate a between-group difference of at least 30 min of aerobic activity and/or one session of resistance training. This would be indicative of behaviour change that is in line with the minimum level of exercise progression prescribed in our intervention and should also allow us to detect differences in maintenance of activity (equivalent to one session per week) amongst those that enter the study already completing some exercise.

The trial team will determine if progression to a larger scale evaluation is warranted based on the criteria and will work together to revise aspects of the protocol if problem areas are identified (e.g. if recruitment is slow the study may still progress if additional recruitment sites can be secured). The process evaluation will be used to inform improvements to the intervention if usability, acceptability or potential for efficacy issues are identified.

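### Adverse events are solicited only at week 9, before the wait-list group starts the programme, so with full uptake at most half of those exposed are systematically assessed for safety

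*Protocol article*

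**What the plan says.** In the protocol article, the Sample size section states that "the enrolment target for this trial is 66 participants, 33 in each arm". It says this number allows the team to "identify feasibility problems (drop out, safety issues etc".) that arise "with a reasonable probability of occurring (i.e. a probability of 10% or greater), with a 95% level of confidence".

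The Pre-established criteria section makes one of the conditions for success: "There is no grade 3+/life threatening or severe adverse events attributed to participating in the intervention". The Abstract lists safety as part of the primary feasibility outcome and gives baseline and week 9 as the measurement times.

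Table 5 (section Waitlist control group) has one adverse-event row, "Common Terminology Criteria for Adverse Events V.5.0 grading criteria". It is ticked for both groups, with week 9 as the only collection point. The Adverse events section describes the same thing: one item in the follow-up questionnaire, plus a request that participants report injuries through the website or by telephone.

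Under Waitlist control group, controls repeat the outcome measures in week nine. Afterwards they are "given access to the eHealth tool for 8 weeks, complete two tele-coaching sessions and receive weekly contact from an exercise physiologist". No later assessment is listed for them.

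**The concern.** The safety criterion concerns events caused by the programme, so the relevant denominator is the people who have used it. In the randomised period that is the 33 intervention participants. The controls then form a second exposed group of up to 33, on the same website with coaching and weekly contact. Their only solicited adverse-event report comes at week 9, before they have started, so it can say nothing about events attributed to the programme.

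For up to half of those eventually exposed, an event therefore comes to light only if the participant volunteers it or it happens to emerge in a contact. The Introduction calls the safety of these techniques in this population unknown, and a finding of zero events feeds the decision on a larger trial. How much a zero count can exclude depends directly on how many exposed people were asked.

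**Working it through.** **Inputs.** Problem probability 10% and confidence 95% (Sample size); 33 per arm, 66 in total (Sample size); success rule of zero attributed grade 3+ events (Pre-established criteria); adverse-event item at week 9 only (Table 5); 8 weeks of wait-list access after week 9 (Waitlist control group).

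**Step 1: the plan's own figure.** The chance of seeing a problem of probability p at least once in n people is 1 − (1 − p)^n. Setting this to 0.95 with p = 0.10:

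- n = ln(0.05)/ln(0.90) = 28.4, so 29 are needed.
- n = 33: 1 − 0.9^33 = 96.9%.
- n = 66: 1 − 0.9^66 = 99.9%.

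The stated property is reproduced on either denominator.

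**Step 2: the margin in one arm.** Usability and satisfaction are measured only in the intervention group (Table 5), and during the randomised period attributed events can arise only there. For these the denominator is 33.

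- n = 29: 95.3%.
- n = 28: 94.8%.

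The property survives the loss of four of the 33 (29/33 = 87.9% observed) and fails narrowly at the fifth.

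**Step 3: exposure against scheduled assessment.**

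| Group | On the programme | Adverse-event item |
|---|---|---|
| Intervention | weeks 1–8 | week 9, after exposure |
| Wait-list | 8 weeks, starting after the week-9 assessment | week 9, before exposure |

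With full wait-list uptake, at most 33 of 66 exposed people (50%) have a scheduled assessment after exposure. If fewer controls take it up, the unassessed share is smaller.

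**Step 4: what zero events excludes.** The one-sided 95% upper bound after zero events in n people is 1 − 0.05^(1/n). Wait-list uptake is not given in the article, so a range is shown.

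| Controls who take it up and are assessed | Exposed and assessed | Upper bound |
|---|---|---|
| 0 | 33 | 8.7% |
| 17 | 50 | 5.8% |
| 33 | 66 | 4.4% |

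**Step 5: chance of meeting the criterion at a given true rate.** The article gives no true rate, so these are assumed values. The probability of zero events is (1 − rate)^n.

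| Assumed true rate | n = 33 | n = 66 |
|---|---|---|
| 2% | 0.98^33 = 51% | 0.98^66 = 26% |
| 5% | 0.95^33 = 18% | 0.95^66 = 3% |
| 10% | 0.90^33 = 3% | 0.90^66 = 0.1% |

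Steps 4 and 5 assume that everyone counted is fully ascertained, that participants are independent, and that the per-person risk is the same in both exposure periods.

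**The case against.** The best defence is that adverse-event capture does not rest on the week-9 item. Participants are told to report injuries by website or telephone, and the Data management and monitoring section sends any adverse event to the steering committee. Neither route is limited by arm or by week. Wait-list participants also have coaching sessions and weekly contact, in which a serious event could well come up. The success criterion itself is not restricted to the intervention arm or to week 9. Wait-list access is offered on ethical grounds after outcome collection has ended, and a condensed article may leave later follow-up to the full protocol.

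Much of this stands. It rules out the inference that wait-list events are left out of the safety count, or that only half of those exposed support the safety conclusion: the article says neither. What remains is the difference between asking and waiting to be told. The weekly contact is given no adverse-event purpose, and Table 5 states week 9 as the collection point, so the schedule is not merely left unmentioned.

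A reader might also infer that the 10%-at-95% property fails at the plan's own 75% data threshold. Carried over to one arm, 75% of 33 is 24.75; with 25 people detection is 92.8%, and the smallest problem detectable at 95% is 11.3%. The documents do not support that transfer. The threshold concerns behaviour change data among all recruited participants, with a similar one for the physical-function subset. It is not set for adverse events or for the intervention arm alone. On its own denominator, 75% of 66 is 49.5, and 49 people give 99.4%. Dropout, the first problem the Sample size section names, can be counted for everyone randomised.

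**Conclusion.** The detection statement is right and needs no correction. Its margin is thin for problems confined to the intervention arm (four participants), and the article states no allowance for loss.

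The point that holds concerns safety ascertainment. Scheduled collection ends before the second exposed group begins, so with full uptake at most half of those exposed are systematically assessed against a zero-event criterion. The information forgone is the difference between an upper bound of 8.7% (33 people) and one as low as 4.4% (66 people). The lower figure requires every control to take up the programme and answer the item, and assumes a similar risk in the two periods; partial uptake falls in between. This is a gap in systematic collection, not an absence of all collection, and it leaves the randomised comparison at week 9 intact. It is worth closing because safety is part of the primary outcome and the exposure is already planned.

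**What to change.** 1. Repeat the existing adverse-event item for wait-list participants at the end of their 8-week access, and add that collection point to Table 5.
2. State that attributed grade 3+ events are reported among all participants exposed to the programme, giving the number exposed, the number who answered the item, and a one-sided 95% upper confidence bound.
3. Keep the randomised week-9 comparison of the two groups as a separate analysis.

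The cost is one extra online item for up to 33 people, sent while they are already in weekly contact, and an amendment through the steering committee and ethics committee. The downside is that the wait-list safety data come about 8 weeks later and have no concurrent control group, so they add to the exposed-population count but not to the between-group comparison.
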